## Methods/design

### Design and sample size

This protocol is for a study of two superiority RCTs with participant preference between the two interventions with 1:1 allocation to either intervention or wait-list within the preferred choice. The randomisation procedure will be web-based and automated; the allocation sequence will be generated and participants randomised using block randomisation by Qualtrics (www.qualtrics.com), the online survey software. Members of the research team involved in the day-to-day management of the study will be blind to block size. Assessments will be completed online by participants at baseline and post-intervention, independent from members of the research team, to reduce risk of bias associated with researcher-administered assessments.

Sample size calculations were conducted using G*Power [13]. The study aims to have 140 participants giving complete data sets at baseline and post-intervention within each part of the study (i.e. aiming for 140 MBCT-L and 140 CBT study completers). Given the pressures on staff time and the online data collection method, it is conservatively assumed that 40% of participants will fail to complete measures post-intervention. This means that we aim to recruit 234 participants into each part of the study.

Sample size calculations are based on an estimated medium between-group effect on post-intervention stress outcomes (Cohen’s *d* = .50) between the intervention and wait-list arms with 90% power and *p* = .05. For MBCT-L, the estimated medium effect size is based on between-group post-intervention effects on stress reported in previous trials of MBIs for healthcare staff [9, 12, 14]. For the CBT stress-management workshop it was not possible to estimate the effect directly based on published trials as previous research has evaluated CBT stress-management interventions running over several sessions. We therefore assume that the effect size will be smaller in the current study than the large effect reported in a meta-analysis of multiple-session CBT stress-management interventions in the workplace [34] and therefore estimate a medium effect size.

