### Participants

Participants will be members of staff working in one of four NHS Trusts in the South of England (three mental health Trusts and one community Trust) with each Trust employing between 2500 and 5000 members of staff. Inclusion criteria are that participants (1) are employed by (or working in an honorary/voluntary capacity for) one of the four NHS trusts, (2) are currently in work (i.e. not currently on sickness absence), (3) have sufficient English language ability to understand intervention information and questionnaire content and (4) are adults (aged 18 years or older). There are no exclusion criteria.

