### Secondary outcomes

#### Sickness absence

Sickness absence data will be obtained from Human Resources departments in the NHS trusts. This will be recorded as the number of sickness absence days taken in the month following the end of the intervention period. Equivalent data from the same 1-month period in the previous calendar year will be obtained as a baseline measure for each participant. Reasons for sickness absence will not be recorded. This is to respect participant confidentiality.

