### Planned data analysis

The intention in providing two interventions is to increase choice and accessibility. The intention is not to compare the effectiveness of the CBT intervention directly with the MBCT-L intervention and any such comparison would be problematic given the potential for selection bias (i.e. participants preferring MBCT-L may differ in a number of ways from participants preferring the CBT workshop). Intervention preference will be reported as the number and percentage of participants choosing each intervention type; however we would urge caution when interpreting these data as participant preferences may be driven by practicalities (e.g. location and dates of available courses) as much as by intervention preference.

Between-group differences at baseline on key demographic variables (age, gender, ethnicity, NHS trust, pay band and years working in the trust) and all outcome measures will be reported for each study. Findings will be reported for both intention-to-treat and per-protocol analyses. Hypotheses will be tested using mixed analysis of variance (ANOVA) for each intervention separately, with time (baseline, post-intervention) as the within-group variable and intervention arm (intervention, wait-list) as the between-group variable. Post-intervention between-group effect sizes (Cohen’s *d*) and 95% confidence intervals will be reported. Interaction effects will be followed up with within-group *t* tests, with Cohen’s *d* effect sizes and accompanying 95% confidence intervals for within-group change.

Qualitative data will be transcribed and thematic analysis will be performed in accordance with the Braun and Clarke [7] protocol. This will involve the researcher leading on the qualitative aspect of the study reading and re-reading transcripts, allocating codes to single units of meaning within each transcript, identifying sub-themes representing lower-order categories of meaning across participants (within CBT/MBCT-L separately) and finally identifying higher-order themes and the relationship between themes and sub-themes (for CBT/MBCT-L separately). This will be conducted under supervision from the lead author. Credibility will be checked through supervision and will be indicated through providing comprehensive extracts from participants to illustrate each theme and sub-theme.

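### The sickness-absence baseline, one month a year earlier, cannot be obtained for recent joiners, and using it as a repeated measure can cost precision

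*Protocol article*

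**What the plan says.** All statements are in the protocol article.

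- **Source and outcome (Sickness absence).** "Sickness absence data will be obtained from Human Resources departments in the NHS trusts". On the outcome: "This will be recorded as the number of sickness absence days taken in the month following the end of the intervention period".
- **Baseline (same section).** "Equivalent data from the same 1-month period in the previous calendar year will be obtained as a baseline measure for each participant".
- **Eligibility (Participants).** Participants must be people who "are employed by (or working in an honorary/voluntary capacity for) one of the four NHS trusts", must be currently in work, and must meet language and age criteria. No minimum service is set, and "There are no exclusion criteria".
- **Analysis (Planned data analysis).** Hypotheses are tested by mixed ANOVA "with time (baseline, post-intervention) as the within-group variable and intervention arm (intervention, wait-list) as the between-group variable". Intention-to-treat and per-protocol results are both promised. Arms will be described at baseline on variables that include "NHS trust, pay band and years working in the trust"; no other use of length of service is stated.

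**The concern.** The baseline is promised for every participant, but the eligibility criteria admit people for whom it does not exist. The analysis then makes the baseline one of the two repeated measurements, so a person without it cannot enter the test even when the outcome month is fully recorded. These people were randomised and have a valid outcome, yet they would be missing from a result labelled intention-to-treat.

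A second weakness lies in the same choice. A single month of absence, a year before the outcome month, may be only weakly correlated with it. Subtracting a weakly correlated baseline adds noise.

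Sickness absence is a secondary outcome, but a prominent one. It heads the list of secondary hypotheses, is presented as the objective indicator of stress, and is described in the Discussion as of particular interest to employers.

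**Working it through.** **The plan's own figures.** The article sizes the trial for stress and gives no figure for sickness absence. Its target is: "The study aims to have 140 participants giving complete data sets at baseline and post-intervention within each part of the study". With 40% not completing, 140 / 0.6 = 233.3, rounded up to 234 recruited per trial, which agrees with the article.

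**Step 1: who has no baseline.** The baseline month lies one year before the outcome month. For the 8-week MBCT-L course, the outcome month starts about 8 weeks after the course begins, so the baseline month starts about 52 − 8 = 44 weeks before the course begins. For the one-day workshop, if the intervention period ends on the day itself, the baseline month starts about 52 weeks before it. A participant who joined after the baseline month had ended has no absence at that Trust to extract; one who joined part-way through has an incomplete month. Someone who moved between two of the four Trusts may have a record at the former one. Nothing in the eligibility criteria keeps recent joiners out.

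**Step 2: what the model does.** With two time points, the time-by-arm interaction is the same test as a two-sample comparison of change (outcome month minus baseline month). A person without a baseline has no change score and contributes nothing.

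**Step 3: how many.** The documents give no share. With an assumed share s, usable pairs = N × (1 − s). The article does not say whether absence is analysed in all 234 or only in the 140 online completers, so both are shown.

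| Assumed share without baseline | Pairs of 234 | Pairs of 140 |
|---|---|---|
| 5% | 222 | 133 |
| 10% | 211 | 126 |
| 20% | 187 | 112 |
| 30% | 164 | 98 |

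**Step 4: direction of any bias.** Length of service at randomisation is a pre-randomisation characteristic. Removing people on it removes them from both arms alike, in expectation. The loss is in precision and coverage; the arm comparison is not biased by it.

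**Step 5: precision of the change score.** Let both months have variance σ² and correlation r.

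- Outcome month alone: σ².
- Change score: 2σ²(1 − r), a ratio of 2(1 − r).
- Baseline as covariate: σ²(1 − r²), a ratio of 1 − r².
- Sample loss equivalent to the change-score ratio: 1 − 1/[2(1 − r)].

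The documents give no r, so these values are assumptions.

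| r | Change score, 2(1 − r) | Equivalent sample loss | Covariate, 1 − r² |
|---|---|---|---|
| 0.1 | 1.8 | 44% | 0.99 |
| 0.3 | 1.4 | 29% | 0.91 |
| 0.5 | 1.0 | none | 0.75 |

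Below r = 0.5 the planned comparison is less precise than ignoring the baseline. Apart from negligible degrees of freedom, the covariate analysis is never worse than ignoring it.

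**The case against.** The case on the other side has five parts.

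1. **Missing values belong to the analysis plan, which is not shown.** This is right as far as it goes, and silence on missing data is not the point here. But the article itself fixes the baseline definition, the eligibility criteria and the model, and those three do not fit together.

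2. **The loss may be small.** Even with 20% lost, 187 of 234 remain, more than the 140 planned completers. At the effect assumed for stress (d = 0.50, which is not an effect on absence days), two-sided power would fall only from 0.97 to 0.93. This stands if absence is analysed in everyone randomised. If it is restricted to the 140 completers, the same share takes power from 0.84 to 0.75.

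3. **The same calendar month guards against season.** This stands for the planned within-group follow-up tests. It does not help the between-arm test, since randomised arms share calendar time.

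4. **A 12-month extract asks for more personal data**, in a study that stresses confidentiality and was already recruiting. This stands, and it makes the longer window a preference subject to permissions.

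5. **Stronger readings go too far.** This stands for each of the following, which a reader might infer:
 - *People without a record are scored as zero days.* The documents nowhere say so; it is only a risk when an HR extract comes back blank.
 - *Honorary and voluntary staff have no HR absence records.* The documents are silent. If it were so, their outcome month would be missing too, which is a different problem from the baseline.
 - *The result is biased toward no difference.* Dropping recent joiners does not do this, and false zeros at baseline would add noise in both arms. Only false zeros in the outcome month would dilute an effect, and new starters are in post by then.

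**Conclusion.** The point holds in a limited form. As written, the baseline cannot be obtained for participants who joined their Trust after the prior-year month, and the mixed ANOVA cannot use them. The consequence is less precision and a narrower intention-to-treat population for one secondary outcome, without bias in the arm comparison from this cause alone. The number affected is unknown, and the shares shown above are assumptions.

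The precision argument is separate and applies to everyone analysed. It rests on equal variances in the two months and on r below 0.5. If r is 0.1 to 0.3, the change-score comparison has 1.8 to 1.4 times the variance of comparing the outcome month alone. At r of 0.5 or above, the change score is no worse than the outcome month alone, although the covariate analysis remains at least as precise.

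**What to change.** - **Model.** Compare sickness days in the outcome month between arms, with prior absence as a covariate and not as a repeated measure.
- **Recent joiners.** Keep participants without a prior record, for example by setting the covariate to a constant and adding a missing-baseline indicator. Whether the record is missing is settled before randomisation, so this does not disturb the arm comparison.
- **Baseline window.** Preferably take prior absence over the 12 months before randomisation, or over time in post if shorter, expressed as a rate, if consent and data permissions allow. If HR supplies it by month, it should also contain the same-month value already planned, which remains available for the within-group tests. The indicator is still needed for very recent starters.
- **No record.** Treat the lack of an HR record as missing, never as zero days, and state that the absence analysis covers participants with HR absence records.

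**Cost.** HR data are requested only at the end of the study, so the change concerns a request not due until then. The extract becomes somewhat wider and permissions must be checked. Any staff without HR records, possibly honorary or voluntary staff (an assumption), leave this one outcome. The model and the wording on who is analysed can be changed without any new data.

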#### Depression

This will be measured using the depression subscale from the short version of the DASS-21 [27]. The depression subscale of the DASS-21 measures the severity of core symptoms associated with depression. Participants are asked to indicate the presence of each symptom over the past week. Responses are given on a 4-point Likert scale, ranging from 0 (never) to 3 (almost always). The DASS-21 depression subscale has been found to have good internal consistency and convergent and discriminant validity [2, 19].

#### Anxiety

This will be measured using the anxiety subscale from the short version of the DASS-21 [27]. The anxiety subscale of the DASS-21 measures the severity of core anxiety symptoms. Participants are asked to indicate the presence of each symptom over the past week. Responses are given on a 4-point Likert scale, ranging from 0 (never) to 3 (almost always). The DASS-21 anxiety subscale has been found to have good internal consistency and convergent and discriminant validity [2, 19].

#### Wellbeing

Positive mental wellbeing will be measured using the 7-item Short Warwick Edinburgh Mental Wellbeing Scale (SWEMWBS) [38]. The SWEMWBS involves rating items on a 5-point Likert scale ranging from 1 (none of the time) to 5 (all of the time). Participants are asked to rate items based on their experience over the past 2 weeks. The SWEMWBS has been found to be highly correlated with the long version of the scale and good construct validity [38].

#### Burnout

This will be measured using the 22-item Maslach Burnout Inventory – Human Services Survey (MBI-HSS) [29]. The MBI-HSS was designed for professionals working in human services such as healthcare and consists of three distinct subscales, emotional exhaustion, depersonalisation, and personal accomplishment. Participants are asked about the frequency with which they have experiences related to the three subscales and items are answered on a 7-point Likert scale, ranging from 0 (never) to 6 (every day). The three subscales of the MBI-HSS has been found to have adequate internal consistency, test-retest reliability and convergent and discriminant validity.

#### Presenteeism

This will be measured using the 3 questions that assess presenteeism, from the Institute for Medical Technology Assessment Productivity Cost Questionnaire (iMTA PCQ) [6]. The overall iMTA PCQ is designed to assess and value productivity losses. The 3 presenteeism questions ask participants (1) if over the past 4 weeks, they worked whilst experiencing physical or psychological problems (yes/no) and if so, (2) how many days at work they were bothered by these problems and (3) how their performance on these days compared to their performance on normal working days. The third question is measured on a 10-point rating scale, ranging from 0 (on these days I could not do anything) to 10 (I was able to do just as much as I normally do). The first 2 questions originate from the short form of the Health and Labour Questionnaire (SF-HLQ) [40] and the third question from the Productivity and Disease Questionnaire (PRODISQ) [22]. The 3 questions have been found to have good test-retest reliability [6].

#### Mindfulness

This will be measured using the 15-item Five Facet Mindfulness Questionnaire (FFMQ-15) [4, 8, 17]. The FFMQ-15 is a short form of the 39-item FFMQ (FFMQ-39) and measures the general tendency to be mindful in everyday life. It includes the same five facets as the long form: observing, describing, acting with awareness, non-judging of inner experience and non-reactivity to inner experience. The factor structure of the FFMQ-15 is consistent with that of the FFMQ-39, there is strong correlation between the total facet scores of the short and long forms, and the two FFMQ versions do not differ significantly from each other in terms of convergent validity [17]. Previous research [3, 17, 42] found that in non-meditator samples, a four-factor hierarchical structure without the “observing” facet provided a superior fit compared to a five-factor hierarchical structure. As it is likely that our current sample has little or no previous meditation experience, “observing” items will be excluded from the total FFMQ-15 score. FFMQ-15 items are rated on a 5-point Likert scale, ranging from 1 (never or very rarely true) to 5 (very often or always true) and will be completed by participants randomised to MBCT-L or wait-list for MBCT-L only.

#### Intervention engagement – MBCT-L participants

MBCT-L participants will be asked to report the following post-intervention: (1) number of MBCT-L sessions attended, not including the orientation session (0–8); (2) average number of days per week engaged in a guided mindfulness practice, not including practice during the group session (0–7); (3) on days when practised, average number of minutes per day of mindfulness practice, not including practice during the group session; (4) ability to bring mindfulness principles into daily life (0–5); (5) ability to actively participate in MBCT-L sessions (0–5); (6) belief in effectiveness of mindfulness in helping to manage stressful situations (0–5); (7) difficulty in finding time to engage in between-session mindfulness practices; (8) satisfaction with the mindfulness teacher leading the course (0–5) and (9) levels of comfort with other group members (0–5). The 0–5 rating scales are all anchored by “not at all” (0) and “extremely” (5).

#### Intervention engagement – CBT participants

CBT workshop participants will be asked to report the following post-intervention: (1) attendance at CBT workshop (no, yes (part of the day), yes (whole day)); (2) satisfaction with the workshop facilitators (0–5) and (3) levels of comfort with other workshop members (0–5). The 0–5 rating scales are all anchored by “not at all” (0) and “extremely” (5).

All outcome measures, with the exception of sickness absence data, which will be requested from HR departments at the end of the study, will be administered at baseline and post-intervention. Demographic data (e.g., gender, age, ethnicity, marital status, education level) will be recorded at baseline only and engagement measures will be administered post-intervention only.

Ten participants from the intervention arm of each RCT, who provide complete data sets at baseline and post-intervention, will be interviewed about their experiences of their intervention by telephone, using an adapted version of the Change Interview [11]. A copy of the Change Interview published by Elliott and Rodgers can be found online [10]. This is a semi-structured interview designed to explore people’s experiences of psychological interventions, focusing on perceived helpful, unhelpful and missing aspects of the intervention. Each interview will take approximately 30 min, will take place over the phone, and will be audio recorded to aid transcription and data analysis.

### Planned data analysis

The intention in providing two interventions is to increase choice and accessibility. The intention is not to compare the effectiveness of the CBT intervention directly with the MBCT-L intervention and any such comparison would be problematic given the potential for selection bias (i.e. participants preferring MBCT-L may differ in a number of ways from participants preferring the CBT workshop). Intervention preference will be reported as the number and percentage of participants choosing each intervention type; however we would urge caution when interpreting these data as participant preferences may be driven by practicalities (e.g. location and dates of available courses) as much as by intervention preference.

Between-group differences at baseline on key demographic variables (age, gender, ethnicity, NHS trust, pay band and years working in the trust) and all outcome measures will be reported for each study. Findings will be reported for both intention-to-treat and per-protocol analyses. Hypotheses will be tested using mixed analysis of variance (ANOVA) for each intervention separately, with time (baseline, post-intervention) as the within-group variable and intervention arm (intervention, wait-list) as the between-group variable. Post-intervention between-group effect sizes (Cohen’s *d*) and 95% confidence intervals will be reported. Interaction effects will be followed up with within-group *t* tests, with Cohen’s *d* effect sizes and accompanying 95% confidence intervals for within-group change.

Qualitative data will be transcribed and thematic analysis will be performed in accordance with the Braun and Clarke [7] protocol. This will involve the researcher leading on the qualitative aspect of the study reading and re-reading transcripts, allocating codes to single units of meaning within each transcript, identifying sub-themes representing lower-order categories of meaning across participants (within CBT/MBCT-L separately) and finally identifying higher-order themes and the relationship between themes and sub-themes (for CBT/MBCT-L separately). This will be conducted under supervision from the lead author. Credibility will be checked through supervision and will be indicated through providing comprehensive extracts from participants to illustrate each theme and sub-theme.

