### Procedure

Recruitment is planned to take place between July and December 2017. The Consolidated Standards of Reporting Trials (CONSORT) diagram showing participant flow through the study is shown in Fig. 1. The study will be advertised to all Trust staff through adverts placed on intranets and staff bulletins. In addition, information about the study will be emailed to all staff. Participants consenting to take part in the study will first choose their preferred intervention. Staff can take part in one of the two studies, but not both. This will be checked to ensure that all consenting participants are enrolled in one of the two studies only. Following consent, participants will be sent a standardised e-mail by the research team containing a link to the baseline assessment measures hosted on Qualtrics based on their selected intervention (Time 0). Upon completion of baseline measures, participants will be randomised to their preferred intervention or to the wait-list for their preferred intervention. They will be sent a standardised e-mail informing them of their allocation and details of their intervention. After participants have completed their intervention or wait-list time period, they will be sent a standardised e-mail asking them to complete post-intervention measures online (Time 1). MBCT-L participants will be sent the link to post-intervention measures immediately after completion of the intervention. CBT participants will be invited to complete post-intervention measures one month after workshop completion. The research team will not be present for any of the online assessments (at baseline and post-intervention); measures will be completed by participants online and in their own time. To promote study retention, where necessary participants will be emailed at weekly intervals for up to 4 weeks with a reminder to complete their post-intervention assessment. Potential errors with data entry will be minimised as data will be entered by participants online.

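### For the self-report outcomes, the named two-time mixed ANOVA does not by itself give the promised intention-to-treat result, and the rule for sending Time 1 measures needs reconciling

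*Protocol article*

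**What the plan says.** **Analysis set and model.** Protocol article, Planned data analysis: "Findings will be reported for both intention-to-treat and per-protocol analyses". The same paragraph fixes the test: "Hypotheses will be tested using mixed analysis of variance (ANOVA) for each intervention separately". The within-person factor has two levels, the measurement before and the measurement after the intervention; the between-person factor is the allocated arm. The article defines neither analysis set.

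**Expected loss.** Design and sample size: "The study aims to have 140 participants giving complete data sets at baseline and post-intervention within each part of the study", and "it is conservatively assumed that 40% of participants will fail to complete measures post-intervention". Then: "This means that we aim to recruit 234 participants into each part of the study".

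**When Time 1 is sent.** Procedure: "MBCT-L participants will be sent the link to post-intervention measures immediately after completion of the intervention". For the other trial: "CBT participants will be invited to complete post-intervention measures one month after workshop completion". Wait-list participants are contacted when their waiting period ends. Randomisation follows the baseline measures, so everyone randomised has baseline data.

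**What completion means.** Under Interventions, completing MBCT-L is defined as attendance at four or more of the eight sessions, and completing the CBT workshop as presence for the full day.

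**What the Time 1 forms allow.** The two Intervention engagement sections accept zero MBCT-L sessions, and no attendance or part-day attendance at the workshop.

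**The concern.** An intention-to-treat analysis keeps all randomised participants in their allocated arm. A mixed ANOVA with a two-level within-person factor needs both values from each person. Someone without Time 1 has no change score and adds nothing to the time-by-arm interaction. With 40% loss planned, the label and the named model do not match for any outcome collected by survey, including the primary one.

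The Time 1 wording adds a second problem. Completion is a defined term. Read with that definition, the Procedure section gives no Time 1 date to an intervention participant who attends two sessions or none, whereas every wait-list participant has one. Outcomes that were never requested cannot be recovered by any analysis.

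At stake is whether the reported effect describes everyone offered the intervention or only those who answered. If answering depends on attendance or perceived benefit in one arm and not in the other, the contrast between responders is no longer a randomised comparison.

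**Working it through.** **1. The plan's own figures.** Inputs from Design and sample size: d = 0.50, 90% power, p = .05, 1:1 allocation, 40% loss.
- Two-sample t test, one-sided: 69.2, rounded up to 70 per arm, total 140. This matches the stated number of completers.
- Inflation for loss: 140 / (1 − 0.40) = 233.3, rounded up to 234. This matches the recruitment target.
- The article does not state sidedness. A two-sided test would need 86 per arm (172 in total), and 70 per arm would give 83.6% power. That is a separate matter and does not bear on this point.

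**2. Who is in the named analysis.**
- Randomised per trial: 234, or 117 per arm.
- With both time points: 234 × 0.60 = 140.4, about 140 (70 per arm if loss is equal).
- Without Time 1: 234 × 0.40 = 93.6, about 94 per trial, or 188 of 468 over both trials.

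**3. What this could do to the estimate (illustration; the documents give no inputs for it).** Let a be the amount, in SD, by which intervention-arm non-responders score worse than that arm's responders. Let b be the same quantity in the wait-list. With 40% missing in each arm and a complete-case d of 0.50:

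d for all randomised = 0.50 − 0.4a + 0.4b

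| Assumption | Calculation | d, all randomised |
|---|---|---|
| Intervention non-responders gain nothing; wait-list loss uninformative (a = 0.50, b = 0) | 0.50 − 0.20 | 0.30 |
| Intervention non-responders gain half; wait-list loss uninformative (a = 0.25, b = 0) | 0.50 − 0.10 | 0.40 |
| Small difference in the intervention arm only (a = 0.10, b = 0) | 0.50 − 0.04 | 0.46 |
| Equal differences in both arms (a = b) | 0.50 − 0.4a + 0.4a | 0.50 |
| Difference in the wait-list only (a = 0, b = 0.25) | 0.50 + 0.10 | 0.60 |

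The last two rows show that the bias can vanish or reverse.

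**4. The Time 1 passages side by side.**
- Towards completers only: the Procedure section speaks of completion in both trials, and Interventions defines that word by attendance.
- Towards everyone: the Time 1 engagement items allow for no attendance. Design and sample size selects interviewees by two separate conditions, complete data and a completed intervention, and the second would be redundant if only completers were surveyed. The Intervention engagement – CBT participants section has the outcome measures given at both time points with no attendance condition.
- If only completers received Time 1, and per-protocol means intervention completers, the intervention arm would contain the same people in both promised analyses.

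The second reading is better supported, but the Procedure wording does not say it.

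**The case against.** The strongest reply is that the article never says cases will be deleted. The same ANOVA can be run on imputed data, and missing-data handling is something a condensed article commonly leaves to the full protocol or the SAP. This stands, and it limits the point. A reader might infer that the trial will not deliver an intention-to-treat result, but the documents do not support that. They support only that the analysis as named does not deliver it unaided. The point rests on what the article does state: the label, the model and the expected loss.

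A reader might also infer that non-attenders are denied the Time 1 survey. The engagement items, the interview criteria and the plan for a separate per-protocol analysis all point the other way, and the article attributes the 40% to time pressure and online collection. What remains is a conflict of wording.

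Sizing on completers and inflating for loss is ordinary practice and no defect, and the article calls 40% conservative, so actual loss may be lower.

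A claim that complete-case analysis must favour the intervention would also go too far. The most stressed wait-list staff may be the ones who do not reply. Finally, sickness absence is taken from HR records, so missing the survey does not remove it.

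**Conclusion.** The point holds in limited form. For the self-report outcomes, including stress, the named analysis is a complete-case analysis of about 140 of 234 randomised per trial at the planned loss, and the intention-to-treat label is not earned unless imputation is specified in a document not shown. Sickness absence is outside the point. The Time 1 wording in Procedure conflicts with the completion definitions read alongside the engagement items and interview criteria, and these sections must be reconciled.

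The count of about 94 per trial follows from the article's own 40%. The effect on the estimate does not. The range of 0.30 to 0.40 against 0.50 assumes that intervention-arm non-responders gain between nothing and half of the responders' benefit, and that wait-list loss is uninformative. Other assumptions leave d unchanged or raise it.

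**What to change.** 1. **Time 1 timing.** State that the survey goes to every randomised participant whatever their attendance: at the scheduled end of the allocated MBCT-L course, or one month after the allocated workshop date, with wait-list timing matched. Recruitment was still open at submission. If some follow-up has already taken place, record which rule was applied.
2. **Primary analysis.** Define intention-to-treat as all randomised participants in their allocated arm. Use a likelihood-based or baseline-adjusted model with multiple imputation by arm from baseline outcomes and demographics. Use attendance in the imputation only if course registers record it independently. The only attendance data the article describes are self-reported at Time 1, so they are missing for exactly the people to be imputed.
3. **Sensitivity.** Imputation from baseline alone adds limited information beyond complete cases. Add a delta-adjusted missing-not-at-random analysis with the shift varied separately by arm, since the direction of bias is unknown.
4. **Labelling.** Report the mixed ANOVA on people with both time points as complete-case.

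The cost is a change to the e-mail trigger, revised analysis wording and more programming. No extra participants or questionnaires are needed. Independent attendance registers, if not already kept, would be an additional collection and are optional.
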